**SERIOUS AES**

SAEs must be recorded during the entire study.

An SAE form should be completed and emailed to the Chief Investigator within 24 hours. However, hospitalisations for elective treatment of a pre-existing condition do not need reporting as SAEs.

All SAEs should be reported to the REC which gave favourable opinion of the study, where in the opinion of the Chief Investigator the event was:

‘related’, i.e. resulted from the administration of any of the research procedures; and

‘unexpected’, i.e. an event that is not listed in the protocol as an expected occurrence

Reports of related and unexpected SAEs should be submitted within 15 days of the Chief Investigator becoming aware of the event, using the NRES SAE form for non-IMP studies. The Chief Investigator must also notify the Sponsor of all related and unexpected SAEs.

The aQIV is subject to additional monitoring. At the Chief Investigator's discretion, side effects of vaccination that are suspected adverse reactions will be reported to the MHRA via its Yellow Card Scheme: [www.mhra.gov/yellowcard](http://www.mhra.gov/yellowcard)

**10.ASSESSMENT AND FOLLOW-UP**

Participants who may be eligible will be identified through access to the NIHR Imperial CRF healthy volunteer database, and through advertising the study across multiple outlets including in the community, in the workplace and online. Written information about the study will be made available on request. Interested potential participants will be invited for a face-to-face screening visit.

**STUDY ASSESSMENT SCHEDULE**

Participants will be followed up according to the study schedule in Table 1. Participants will attend a screening visit at the study site, and they will be asked to provide proof of identity at the visit. Written informed consent will be obtained from participants before undergoing study procedures. The visits in the study assessment schedule are a screening visit (V1), an enrolment visit at which the first FNA will be performed (V2), a vaccination visit (V3), a follow-up visit at which the second FNA will be performed (V4) and a final follow-up visit (V5). In addition, participants will be contacted by telephone (V2a) a few days after the first FNA at V2. For a small number of participants in cohort 2 (up to n=6) there will be an option of a third FNA visit at 6 weeks post vaccination.

**PROCEDURES DURING THE SCREENING PERIOD****Informed consent**

Participants will be given written information about the study, the sampling procedures, the vaccine and the data collection and sharing. Those who wish to proceed will be asked to sign a witnessed consent form before undergoing screening investigations. A copy will be provided to the participant, and one kept in the study file according to local SOPs.

**Eligibility**

Eligibility will be assessed by means of demographics, medical history, medications, physical examination and laboratory investigations. Screening examination will include clinical observations (blood pressure, temperature and pulse), height and weight, inspection of the FNA sites (skin and an assessment of lymph nodes). Symptom directed examination will be at discretion of the physician. During the study, participants should not take any aspirin or medication that may increase risk of bleeding 7 days before each procedure. Enrolment of participants who usually take these medications for any reason will be at the discretion of the investigator.

**Clinical laboratory investigations**

Tests to be conducted at screening are in Table 1 and its footnotes. Individuals with laboratory abnormalities at screening considered clinically significant by the investigator and likely to interfere with the conduct of the study will not be eligible for enrolment.

**PROCEDURES AT ENROLMENT AND FOLLOW UP****Fine needle aspiration**

Participants will undergo fine needle aspiration of suitable axillary lymph nodes at enrolment, and again after receiving immunisation. The process for sampling is described in Appendix 2.

**Injection**

Intramuscular injection of seasonal influenza vaccine into the deltoid muscle of participants' choice will be according to standard clinical practice. The arm injected will be recorded. Prior to receiving the injection, the participant will have vital signs measured. A temperature of 37.8 °C or above would prevent injection on the day. Introduction of new concomitant medications such as immunosuppressive medications, or new acute illness may prevent injection on the day at discretion of the investigator. Participants will remain at the study site for at least 30 min after injection, for safety reasons.

**COVID-19**

Participants will be asked about COVID-19 symptoms at every visit. Presence of highly likely COVID-19 symptoms in the opinion of the investigator will trigger a PCR or lateral flow test (which can be self-taken) in accordance with NHS guidance. The visit will be delayed until the result is known. A negative response will allow the visit to continue per protocol.

A positive response will delay the visit until the NHS stipulated period of isolation is complete.

### **Receiving an authorised COVID-19 vaccine**

It is anticipated that volunteers entering the study will already have received a full course of COVID-19 vaccination as defined by the Green Book chapter 14a. If they have not done so, volunteers are encouraged to receive a full course of COVID-19 vaccination at least 28 days before enrolling onto the study. Volunteers who enrol and subsequently become eligible for an authorised COVID-19 vaccine booster through standard NHS care can receive the vaccine during the study. A gap of at least 28 days either side of an FNA is preferred but where there is clinical imperative a shorter gap is acceptable. Where a COVID-19 vaccine is scheduled near to an FNA, the FNA should occur before the vaccination where possible.

### **PROCEDURES FOR ASSESSING SAFETY**

Seasonal influenza vaccine is a widely used licensed product with a well described post-licensure safety profile. Detailed information on safety data available for aQIV is available in section 2 study design and in Appendix 1. aQIV is subject to additional monitoring and healthcare professionals are asked to report any suspected adverse reactions via the Yellow Card Scheme:

[www.mhra.gov.uk/yellowcard](http://www.mhra.gov.uk/yellowcard)

Fine needle aspiration is a standard and well-tolerated clinical technique. Safety assessments on the study will be limited to assessing the safety and tolerability of study procedures purely in order to safeguard the wellbeing of participants, in accordance with the experimental medicine framework for the study. There are no safety-related objectives of the study.

### **PROCEDURES FOR ASSESSING IMMUNE RESPONSES**

Whole blood and lymph node samples will be collected to assess cellular immunity and humoral immunity and DNA extracted for genomic analysis such as HLA typing. Whole blood will be collected at Visits 2 and 3-5. Lymph node samples will be collected at Visits 2 and 4. Pax gene tubes for assessing the RNA transcriptome will be collected at Visits 3 and 4.

### **INCIDENTAL FINDINGS**

An incidental finding is one that has potential health or reproductive importance, which is discovered unexpectedly but is unrelated to the purpose or aims of the study e.g., an abnormal laboratory safety test result. Local site (NIHR Imperial CRF) procedures will be followed. Depending on the nature of the finding, the subject might have to be withdrawn or vaccination or sampling discontinued, and his/her GP informed.

### **LOSS TO FOLLOW-UP**

Participants who do not attend scheduled visits will be contacted according to local standard procedures which includes contacting through telephone and NHS text. Every reasonable attempt will be made to maintain contact with participants during their participation in the study.

**STUDY CLOSURE**

The study will be closed when all participants have completed their final follow-up visit and assessments are completed including those to determine resolution of any adverse events and the data recorded and locked.

**11. QUALITY ASSURANCE AND CONTROL**

Quality assurance (QA) includes all the planned and systematic actions established to ensure the study is performed and data generated, recorded and reported in compliance with the principles of GCP and any regulatory requirements. Quality control (QC) includes the operations to ensure that requirements for the study activities are fulfilled.

**SAFETY AND RIGHTS OF PARTICIPANTS**

Participants will be donating tissue and undergoing immunisation using procedures that are commonly undertaken for patients in the NHS. Confidential information will be kept allowing safety assessments to be made throughout the study.

**PROJECT DESIGN AND RELIABILITY**

A feasibility study is published, led by the Chief Investigator (EAVI2020\_01 FNA sub study). This study has indicated that lymph node sampling is feasible, safe and with ample yields to be undertaken as part of human vaccine research.

**CLINICAL DATA RECORDING AND MONITORING**

Worksheets for the study will be created for each study visit. Completed worksheets will undergo regular QC assessments by the study clinical team. Data will be stored by means of an electronic database using REDCap or similar software system.

**AUDITS**

The study may be subject to audit by Imperial College London, under its remit as sponsor, and other regulatory bodies to ensure adherence to GCP and the UK Policy Framework for Health and Social Care Research.

**12. STATISTICS AND DATA ANALYSIS**

Thirty volunteers will be enrolled.

Ultrasound images will be collected using the software provided with the US machine operating system. These may be securely shared for storage on a secure password protected computer as anonymised images using the US applications such as ApliGate, developed by Canon for the secure

sharing of images. Ultrasound images will be stored with the unique study identifier for each participant, the date of the scan and the initials of the person performing the examination.

For single cell RNA-seq experiments, we anticipate capturing ~3,000-5,000 cells per sample after quality control (QC) and filtering. Sequencing, batch correction, filtering, QC, doublet removal, ambient RNA correction and correction for multiple testing will be performed according to single-cell RNA-seq best practices using established pipelines and tools (e.g. <https://github.com/[name]>; COMBAT Consortium 2022). Statistical and outcome measures will typically be assessed through ANOVA, Wilcoxon rank, and Fisher exact tests. Dimensionality reduction processes will be used to understand data structure and to identify clusters and cell types for statistical testing. Differential cluster abundance and differential gene expression using pseudobulk counts will be performed using relevant edgeR packages and applying a Benjamini-Hochberg multiple testing correction. Power calculations for single-cell RNA-seq data analysis are based on relevant available data (e.g., Turner et al. 2020), and for assessing differential abundance and gene expression, for instance, we estimate that n=10 individuals per group are required to have >80% power to detect 30% differences between longitudinal samples (pre and post vaccination), with a false discovery rate of 5%. Given that there is expected variation in sample yield after fine needle aspiration which may be anatomically determined, there is a 50% overage in each group to allow for this and for any participants lost to follow up bringing the total to n=30.

Single-cell repertoire analyses will be performed as previously described. Briefly, T cell receptor (TCR) and B cell receptor (BCR) outputs from CellRanger will be further filtered and processed to remove homotypic doublets and low-quality droplets and annotated using IMGT. Single-cell TCR clonality measurements will include Shannon diversity calculation using the entropy R package, and mean clone size estimation by bootstrapped down-sampling. Single-cell BCR clonality measurements will include clonal expansion index calculation based on the Gini index of the number of total BCRs per clone, whilst the clonal diversification index is calculated as the Gini index of the number of unique BCRs per clone.

For bulk sequencing, standard pipelines will be used for data processing (COMBAT Consortium 2022). Principal component analysis will be used for initial analyses of the normalised and filtered data. Differential expression analysis of the normalised data will be performed using the limma R package for example, with pathway enrichment analysis being performed using the Reactome pathways via the XGR R package with Fisher's exact test. Weighted gene correlation network analysis will be applied to identify modules of highly correlated genes. Bulk repertoire analyses will include filtering for base quality amongst other quality control checks, followed by TCR chain/Ig isotype frequency estimates and usage, CDR3 length characterisation, and somatic hypermutation and BCR class-switching analyses.

For flow cytometric analyses, data will be analysed using FlowJo, with appropriate control/validation with non-specific isotype controls and beads to ensure stable equipment calibration over time, as well as use of gating templates. For functional/serological analyses, assays will be performed in duplicate or triplicate with appropriate repeat experiments to ensure reproducibility of findings. Appropriate tests (e.g., t-tests, Wilcoxon rank-sum tests) for assessing inter-group differences will be performed using R, python or GraphPad Prism as required.

Data generated and all appropriate documentation will be stored for a minimum of 10 years after the completion of the study, including the follow-up period.

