## **STUDY AIM, OBJECTIVES AND OUTCOME MEASURES**

The aim of the study is to investigate human immune responses in lymph node cells before and after immunisation with a seasonal influenza vaccine

Primary objective: To generate a single cell atlas of lymph node cells before and after immunisation with seasonal influenza vaccine.

Secondary objective: To compare serum antibody responses before and after immunisation.

Exploratory: To compare immune responses in various immune compartments (e.g., blood and lymph nodes) against antigens including influenza before and after immunisation to help inform vaccine development and testing across different ethnicities.

Capacity building and training: To build capacity with respect to staff expertise and resource between the three partner institutions to support this project and future similar research.

Outcome measures may include but are not limited to the following assays:

1. Single cell RNA sequencing analysis of LNC and matched paired PBMC
2. Binding ELISA specific for influenza/A antigens e.g., haemagglutinin
3. Intracellular cytokine secretion or activation induced marker assay of PBMC and LNC
4. Genotypic assays such as HLA-testing.

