## **7. STUDY DESIGN**

Interventional experimental medicine study using a model vaccine, seasonal influenza vaccine, as a probe to stimulate the immune system in vivo with sampling to collect serum, plasma, PBMC and LNC at specified time points pre and post immunisation. The study is single arm, non-randomised and open label.

Duration: Three years

Number and type of subjects: Thirty healthy adult volunteers of African or Asian ancestry will be enrolled. Participants may enrol into either cohort 1 (influenza season 2022-2023) or cohort 2 (influenza season 2023-2024).

Study intervention: A single dose of a licensed seasonal influenza vaccine will be administered intramuscularly into the deltoid muscle. See Appendix 1 for (2021-2024) recommendations for seasonal influenza vaccines in the UK.

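### N=30 rests on two groups of 15 that the protocol never names and that its enrolment rules do not deliver, so the stated per-group power is not secured

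*Protocol*

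**What the plan says.** Section 12 of the protocol gives the only sample-size justification. It states that "we estimate that n=10 individuals per group are required" "to have >80% power to detect 30% differences", and the contrast meant is "30% differences between longitudinal samples (pre and post vaccination", at a 5% false discovery rate. Because aspirate yield varies, "there is a 50% overage in each group to allow for this and for any participants lost to follow up", which brings the total to 30.

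Section 7 describes a single-arm, non-randomised study. On numbers it says only "Thirty healthy adult volunteers of African or Asian ancestry will be enrolled" and "Participants may enrol into either cohort 1 (influenza season 2022-2023) or cohort 2 (influenza season 2023-2024". The inclusion criteria in Section 8 accept either ancestry. The withdrawal criteria, also in Section 8, allow replacement of people who withdraw or cannot complete the schedule, without reference to any group. Section 6 includes an exploratory objective on immune responses before and after immunisation, "to help inform vaccine development and testing across different ethnicities". Section 12 also plans tests for differences between groups, again without saying which groups.

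**The concern.** A per-group sample size has meaning only if the groups are defined and recruitment delivers them. Here the total holds only with two equal groups, in a study that has one arm. Two two-level splits are available: African or Asian ancestry, and cohort 1 or cohort 2 by season. Neither has a target, minimum or cap. A 24/6 split would break no written rule, yet the smaller group could not reach the 10 that Section 12 calls for.

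Two things are at stake. The first is the stated power within each group. The second is the reading of any exploratory ancestry contrast. Nothing balances ancestry across the two seasons, and Section 20 records that the vaccine was updated for 2023-2024. If the ancestries fall mainly in different seasons, an ancestry difference cannot be told apart from a difference in season or vaccine year.

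This cannot be left to an analysis plan, because who is enrolled is settled at recruitment.

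**Working it through.** **1. The plan's own total.** Inputs from Section 12: n = 10 per group, overage 50% in each group, total 30. With G groups, total = 10 × 1.5 × G.

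| G | 10 × 1.5 × G | 10 / (1 − 0.5) × G |
|---|---|---|
| 1 | 15 | 20 |
| 2 | **30** | 40 |
| 3 | 45 | 60 |

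Only G = 2 with 15 per group gives 30. Dividing by (1 − 0.5) never does. Pre and post cannot be the two groups: the same people give both samples, and the text counts individuals.

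**2. What the overage tolerates.** Loss allowed in a group of m enrolled, keeping 10 evaluable: 1 − 10/m.

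| Split | Tolerated loss, smaller group |
|---|---|
| 15/15 | 1 − 10/15 = 33% |
| 12/18 | 1 − 10/12 = 17% |
| 10/20 | 1 − 10/10 = 0% |
| 9/21 or worse | 10 cannot be reached |

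**3. How likely an imbalance is.** The protocol gives no recruitment mix, so a range is assumed. With X ~ Binomial(30, p), P(smaller group < 10) = P(X ≤ 9) + P(X ≥ 21):

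- pool 50:50: 4%
- pool 60:40: 18%
- pool 70:30: 59%

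**4. Chance that both groups reach 10 evaluable.** Each participant is assumed to give an evaluable pre/post pair independently with probability q, and replacement is ignored. Without a cap: Σₓ P(X = x) · P(Bin(x, q) ≥ 10) · P(Bin(30 − x, q) ≥ 10). With a cap: P(Bin(15, q) ≥ 10)².

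| q | 50:50, no cap | 60:40, no cap | 70:30, no cap | 15/15 |
|---|---|---|---|---|
| 70% | 34% | 24% | 7% | 52% |
| 80% | 65% | 47% | 16% | 88% |
| 90% | 86% | 68% | 28% | >99% |

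**5. Power when a group falls short.** Section 12 gives no dispersion and no per-test error rate, so its power figure cannot be recomputed. As an illustration, take the standardised change that gives exactly 80% power at n = 10 in a two-sided paired t test. It is 0.996 at α = 0.05 and 1.866 at α = 0.001, the latter a stand-in for a stricter multiplicity threshold.

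| Evaluable pairs | α = 0.05 | α = 0.001 |
|---|---|---|
| 10 | 80% | 80% |
| 8 | 68% | 52% |
| 6 | 50% | 21% |
| 20 (both groups pooled) | 99% | >99% |

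On the same basis, a between-group difference in change of that size, with 10 against 10 evaluable, has about 56% power at α = 0.05 and 60% at α = 0.001.

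**The case against.** The strongest reply is that no stated primary or secondary objective depends on the split. The primary objective is an atlas before and after immunisation, the secondary is antibody before against after, and the power sentence concerns longitudinal samples. That stands: pooled over all participants, 20 evaluable pairs have about 99% power on the back-solved effect.

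A second reply is that no African-versus-Asian contrast is stated as an objective, let alone claimed as powered. The exploratory objective compares responses before and after immunisation and mentions ethnicities as an application. Section 6 sets the gap against a literature dominated by white European cohorts, which a combined African and Asian dataset also addresses. This stands too. Ancestry is the likely meaning of group, given the study's title and rationale, but season cohort is possible, and the sponsor must say which. The gap is the same either way, since neither split has numbers.

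Third, the probabilities depend on assumptions. Section 8 allows replacement, which would soften losses, and Section 11 reports ample yields from a feasibility study. This is why ranges are shown. But replacement is not tied to a group, so it need not repair the smaller one.

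A reader might point to the 86% chance, at a 50:50 pool, that the split is not exactly 15/15. That overstates the harm: 14/16 counts as a miss, although the smaller group can lose four and keep 10. A reader might also infer that batch correction would remove or create an ancestry effect. That would need near-complete alignment of ancestry with batch, which the protocol does not show. Batch composition and model terms may also sit in a laboratory or analysis plan.

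**Conclusion.** The point holds as a defect in the sample-size basis and should be fixed. The arithmetic of 30 is right, but it presupposes two groups of 15 that the protocol neither names nor secures. At an evenly mixed pool, enrolling fewer than 10 in the smaller group is unlikely (4%), but at 70:30 it is more likely than not (59%). With 80% evaluable, the chance that both groups reach 10 is 65% down to 16% without a cap as the pool moves from 50:50 to 70:30, against 88% at 15/15. These figures rest on assumed pools, assumed evaluability and no replacement; the power figures rest on a back-solved effect.

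It would be tempting to conclude that the primary objective is underpowered, or that a planned ancestry comparison has lost its power. The protocol supports neither: the pooled pre/post analyses are unaffected, and no between-ancestry power was ever claimed. What is affected is the per-group power statement and any exploratory ancestry contrast, which could also be confounded with season.

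**What to change.** - **Section 12:** the sponsor confirms and names the two groups (ancestry is likely; season cohort is the alternative) and states 15 enrolled and at least 10 evaluable in each. It also says that between-ancestry contrasts are exploratory, not powered, and adjusted for season cohort.
- **Sections 7 and 8:** cap enrolment at 15 per group, replace withdrawals within the same group and, as far as open places allow, recruit both ancestries in each season.
- **If cohort 1 is already unbalanced:** forcing an exact 15/15 through cohort 2 could itself align ancestry with season. For example, a 10/2 cohort 1 would need 5/13 in cohort 2. Put at least 10 evaluable per group, with both ancestries present in each season, ahead of exact balance. Otherwise, restate the power as applying to the pooled pre/post comparison only.

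The cost is a short amendment to three sections and no increase in the planned 30. The last places may fill more slowly. The caps help only while places remain open; naming the groups and restating the power can be done at any time.
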